### *Consent*

The participants must personally sign and date the latest approved version of the Informed Consent form before any study specific procedures are performed.

Written versions of the Participant Information Sheet and Informed Consent will be presented to the participants detailing the exact purpose and nature of the study, what it will involve for the participant, the known possible risks and benefits involved in taking part. It will be clearly stated that the participant is free to withdraw from the study for any reason without prejudice to future care, without affecting their legal rights, and with no obligation to give the reason for withdrawal.

The participants will have this information long enough to consider before making an informed decision. The maximum timeframe is two weeks after the initial screening meeting with the CI. Participants will also have the opportunity to question the CI or other independent parties to decide whether they will participate in the study. Written Informed Consent will then be obtained by means of participant dated signature and dated signature of the CI who will present and obtain the Informed Consent. Potential participants might express interest when the recruitment stage of the study will be completed. They will still have the opportunity to have an initial/ screening discussion with CI and with their consent their contact details will be retained by the CI for future research opportunities with their consent. A copy of the signed Informed Consent will be given to the participant. The original signed form will be retained at the study site. The health professional who referred the participant to the study will be informed verbally by the CI that their service user is taking part in the study.

### ***Risks, burdens and benefits***

No serious adverse events are expected as a result of the study design and procedures. However, incidents might take place during the course of the study and the implementation of the psychological intervention:

- Participants might find the participation in a group intervention distressing and tiring.
- Participants might find the quantitative data collection process burdensome.
- Participants might not be able to attend the individual qualitative interviews.
- The group facilitator and the supervisor might make the decision that one or more participants cannot engage into the group intervention with the rest of the members.

The intervention and the study processes have been designed in a way that they respect the participants' needs and characteristics. The research team will follow the participants' pace and will take under consideration factors such as cognitive and physical fatigue in the intervention implementation and data collection processes. Following the PPI involvement input, the intervention and data collection processes will take place online and will be implemented in a flexible way to accommodate participants' needs. Therefore, should any participant miss a session during the intervention implementation because of health issues they will still have the opportunity to continue taking part in the intervention and the study.

Should any of the above adverse events occur, the participants have the right to withdraw from the study without having to justify their decision. If a participant withdraws, the CI will arrange for a check – in meeting with them if they accept the invitation and support resources will be provided to all participants in the Participant Information Sheet. Moreover, all data from participants that withdraw from the study will not be used in the analysis and will be destroyed along with any personal details.

The benefits for participants entail:

- It is aspired that participants will experience the benefits of the intervention in their experience and management of MS, their quality of life and emotion regulation.
- Taking part in a novel group psychological intervention which has been developed by people with MS' accounts of needs and preferences, psychotherapy theory and consultation with practitioners.
- Contributing to ameliorating and finalising the intervention protocol which will be disseminated to patients and practitioners involved in the care of people with MS.
- Participants voices will be heard in terms of how they experience their MS and the psychological intervention through the qualitative processes of collection of data which will provide significant insights into the complexity of the disease and the effects of the intervention as well as future research in the field.

The research study and intervention have been developed based on a patient – centred approach and all procedures have been designed in a way that they protect the participants from the above adverse events and facilitate the benefits for them. Following PPI involvement input, no major amendments were suggested and the members agreed with the suggested risks and benefits. Their recommendation was to ensure that the benefit of participants experiencing the benefits of the intervention in their experience and management of MS should be first in the list.

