The novel intervention MyMS-Ally developed for the current project adopted a process – based approach (Hofmann & Hayes, 2019). Intervention techniques and processes were informed by aspects of established therapeutic approaches as they have been found effective for people with MS based on previous research conclusions. In addition to this, the goal of the current research project is to move away from theory – based interventions and towards a patient – led perspective of intervention development and implementation. We followed the trend in recent literature on clinical therapy processes to move from nomothetic to idiographic approaches of research and intervention (Hofmann & Hayes, 2019). As we have been developing MyMS-Ally group psychological intervention, our aspiration has been to establish processes that correspond to procedures, needs and characteristics of people with MS (Hofmann & Hayes, 2019). Thus, the structure of this intervention has also been based on what people with MS have found significant, helpful and beneficial in their accounts of their experience of psychological interventions they have engaged into ([name] et al., 2022). The themes represented the change processes from the people with MS’ perspective as they related them to intervention processes. These themes guided the development of the novel psychological group intervention MyMS-Ally.

Following the systematic development of the intervention, it needs to be tested carefully through pilot feasibility and acceptability studies in order to address uncertainties and make appropriate modifications before further evaluation of the intervention (Medical Research Council Guidance). The current study will provide valuable information on how the intervention will be appraised by participants that take part, on helpful and unhelpful aspects of the intervention based on the participants’ experiences and accounts as well as the feasibility of implementation of the intervention in the context of the service. Moreover, adherence to outcome measures and study processes will also be assessed which will give valuable information for the design of the consequent evaluation study (Craig et al., 2008).

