### ***Data collection***

Feasibility and acceptability of the processes of the novel group intervention MyMS-Ally will be explored mainly through the qualitative interviews. The participants will attend three qualitative semi-structured interviews:

1. At baseline, before commencement of the intervention: This interview will focus on the experience of their Multiple Sclerosis and the expectations they have from MyMS-Ally group intervention (prospective acceptability, Sekhon et al., 2017).
2. At the end of the intervention (at the end of the 8 sessions): This interview will focus on satisfaction, on helpful and unhelpful aspects of the intervention as they experienced them, what facilitated them to complete the programme and any impact they perceived the intervention had on their experience and management of their Multiple Sclerosis (Sekhon et al., 2017).
3. At three months follow – up: This interview will focus on their experience of MyMS-Ally intervention and the impact it might have on their experience and management of their Multiple Sclerosis.

Interviews are expected to last approximately one hour and they will take place online on a platform with encryption where recordings are possible (Microsoft Teams) and stored on the CI's university (UWE) onedrive in a password protected folder.

Additional indicators will be recorded in order to explore further the feasibility and acceptability of MyMS-Ally intervention (Saracutu et al., 2018):

- Number of people with MS referred by the health and mental health professionals of the service.
- Number of people with MS attending the screening meetings with the Chief Investigator.
- Time taken to complete the questionnaires and missing data.
- Follow up responses (1 month and 3 months follow up).
- Number of sessions attended by the participants.
- Feedback from MyMS-Ally group intervention facilitator.

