## Risks, Burdens and Benefits

No serious adverse events are expected as a result of the study design and procedures. However, incidents might happen during the course of the study and the implementation of the psychological intervention:

- Participants might find the participation in a group intervention distressing and tiring.
- Participants might find the quantitative data collection process burdensome.
- Participants might not be able to attend the individual qualitative interviews.
- The group facilitator and the supervisor might make the decision that one or more participants cannot engage into the group intervention with the rest of the members.

The intervention and the study processes have been designed in a way that they respect the participants' needs and characteristics. The research team will follow the participants' pace and will take under consideration factors such as cognitive and physical fatigue in the intervention implementation and data collection processes. Given COVID restrictions, data collection processes will take place online. The processes will be discussed in the PPI involvement focus group.

Should any of the above adverse events occur, the participants have the right to withdraw from the study without having to justify their decision. If a participant withdraws, the CI will arrange for a check – in meeting with them if they accept the invitation and support resources will be provided to all participants in the Participant Information Sheet. Moreover, all data

from participants that withdraw from the study will not be used in the analysis and will be destroyed along with any personal details.

The CI, the independent researcher as well as the group facilitator will be assessing the risk for the participants. Should the risk becomes high for any of the participants in the course of the intervention implementation and the study, the CI will notify the health professional that referred the participant to the study. This is the only occurrence that confidentiality will be breached to ensure the participants' safety and wellbeing.

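### Destroying all data of participants who withdraw removes the most informative cases from the post-consent feasibility and acceptability results, which are then likely to look too favourable

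*Protocol*

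**What the plan says.** The Protocol, Summary of Main Issues, subsection Risks, burdens and benefits, states that "all data from participants that withdraw from the study will not be used in the analysis and will be destroyed". The later section Risks, Burdens and Benefits repeats the rule: data "from participants that withdraw from the study will not be used in the analysis and will be destroyed along with any personal details". Neither place makes an exception for sessions already attended, questionnaires or interviews already completed, recorded incidents, or the fact and timing of the withdrawal. The rule is automatic and does not depend on a request for erasure.

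Both sections first list possible incidents: distress or tiredness from the group, burden from the questionnaires, inability to attend interviews, and a decision by the facilitator and supervisor that someone cannot take part with the others. The text then continues: "Should any of the above adverse events occur, the participants have the right to withdraw from the study without having to justify their decision".

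The Principal question/objective section counts adherence to the intervention and to the study processes as part of feasibility. The Scientific justification section adds that "adherence to outcome measures and study processes will also be assessed", to inform the design of the next study. Under Data collection, the interviews are the main source. The additional indicators are referrals, screening meetings attended, questionnaire time and missing data, follow-up responses at one and three months, "Number of sessions attended by the participants", and facilitator feedback. A count of withdrawals is not on that list.

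**The concern.** A feasibility and acceptability study learns most from the people for whom the intervention or the data collection did not work. The protocol itself ties withdrawal to distress, burden and non-engagement, so those who withdraw are unlikely to be a random subset. Under the rule, what they contributed before leaving goes. The remaining attendance, follow-up, missing-data and interview results describe only people who did not withdraw, and the next study would be planned on them. The loss is permanent: no analysis plan, however careful, can recover data that have been destroyed.

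**Working it through.** The protocol states no retention, withdrawal or power figure, so there is nothing of its own to reproduce. The group size of 5-6 is justified by group interaction and patient input, not by a formula. The effect of the rule can be worked out directly.

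**Inputs from the protocol:** 5-6 participants per group (Recruitment and Participants sections), 8 sessions, follow-up at one and three months. More groups are possible if interest allows.

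**Assumed, because the protocol is silent:** the number withdrawing, w; every remaining participant responds; only remaining participants' data enter the calculation.

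**Follow-up response.** With n consenting, the proportion on the full denominator is (n − w)/n. On remaining participants only it is (n − w)/(n − w) = 100% for any w below n. Intervals are exact (Clopper-Pearson) 95%.

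| n | w | All who consented | Remaining only |
|---|---|---|---|
| 6 | 1 | 5/6 = 83.3% (35.9-99.6) | 5/5 = 100% (47.8-100) |
| 6 | 2 | 4/6 = 66.7% (22.3-95.7) | 4/4 = 100% (39.8-100) |
| 6 | 3 | 3/6 = 50.0% (11.8-88.2) | 3/3 = 100% (29.2-100) |
| 5 | 1 | 4/5 = 80.0% (28.4-99.5) | 4/4 = 100% (39.8-100) |
| 5 | 2 | 3/5 = 60.0% (14.7-94.7) | 3/3 = 100% (29.2-100) |

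Each withdrawal is 1/6 = 17% to 1/5 = 20% of a single group. With two groups of six it would be 1/12 = 8%.

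**How likely the rule is to matter.** With an assumed, independent withdrawal risk p per person, the chance of at least one withdrawal is 1 − (1 − p)^n. For n = 6 and p = 10%, 20%, 30% this gives 46.9%, 73.8%, 88.2%. For n = 5 it gives 41.0%, 67.2%, 83.2%.

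**Sessions attended.** Suppose remaining participants attend 7 of 8 and each leaver attended s sessions. The mean over all six is (7(6 − w) + s·w)/6.

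- w = 1, s from 1 to 4: 36/6 = 6.0 to 39/6 = 6.5, against 7.0 on remaining participants only.
- w = 2, s from 1 to 4: 30/6 = 5.0 to 36/6 = 6.0, against 7.0.
- w = 1, with a leaver who attended all 8 and withdrew during follow-up: 43/6 = 7.2, so here the rule lowers the mean slightly.

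For follow-up response, the direction is arithmetic once only remaining participants are counted. For attendance, and likewise for acceptability, it depends on leavers having fared worse. The incident list makes that likely but does not prove it.

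**The case against.** Several stronger readings are tempting, and the document does not support them.

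- **All feasibility results are biased upward by rule.** Referral and screening counts precede consent and are untouched, and facilitator feedback is at most partly affected. The direction for attendance and acceptability is likely rather than certain, since people may withdraw for any reason and need not give one.
- **Everyone who found the intervention unacceptable disappears.** The rule reaches only those who withdraw from the study. A participant who misses a session for health reasons may continue, and blank items, unanswered follow-ups or a critical interview from someone who stays are all kept.
- **The report must show 100% retention.** Retention is not a listed indicator, and nothing says that the number recruited is erased. A report of six recruited and four analysed would disclose the loss. The 100% figures hold only if the denominator is also restricted.
- **Harm results are suppressed.** No harm endpoint is defined. Participant protection runs separately, through a check-in meeting after withdrawal and notification of the referring professional when risk is high. What is lost is the incident record in the study data.
- **The closing interview is built for completers.** It does ask "what facilitated them to complete the programme", but the same item also asks about satisfaction and about what did not help.

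It is also fair to say that the study is a small exploratory pilot with no progression threshold that the bias could flip, and that the rule is meant to respect participants. These points narrow the claim. They do not restore the discarded attendance, questionnaires and interviews, and the right to withdraw does not require automatic destruction: data are already held under pseudonyms, and erasure on request can remain.

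**Conclusion.** The concern holds for indicators collected after consent: sessions attended, follow-up responses, missing data and the acceptability interviews. The rule conflicts with the primary objective because it removes evidence on non-adherence and poor acceptability from the people most likely to supply it, and the remaining results are likely to be too favourable. The size cannot be fixed from the protocol, which gives no withdrawal rate. If all remaining participants respond and only they are counted, the overstatement of follow-up response is about 17 percentage points with one withdrawal in six and 33 with two. At assumed risks of 10% to 30% per person, at least one withdrawal in a group of six has a chance of about 47% to 88%. Even if a bare count of withdrawals survived, what those participants did and said would not.

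**What to change.** Replace the sentence in both risk sections, and align the participant information sheet and consent form with it:

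- Pseudonymised data collected up to withdrawal are kept and analysed by default, unless the participant asks for erasure. In that case only the aggregate number of withdrawals is kept. Individual details such as stage or reason should not be retained then, because in a group of 5-6 they could identify the person.
- Distinguish stopping the sessions from withdrawing from data collection. Those who only stop sessions may, if willing, complete the questionnaires and interviews already planned.
- Report the number and timing of withdrawals, with timing only for those who have not asked for erasure.
- Use all who consented as the denominator for attendance and follow-up response. Where erasure leaves a session count unknown, say for how many.

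The cost is a wording change to the protocol and consent documents, best made before anyone consents, and some care in handling people who stop sessions but stay in data collection. The small downside is that participants accept at consent that data already given are kept by default.

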### ***Confidentiality***

The minimum necessary person – identifiable information will be collected for the purposes of the study. The study will comply with the General Data Protection Regulation (GDPR) and Data Protection Act 2018, which require data to be de-identified as soon as it is practical to do so. The processing of the personal data of participants will be minimised by making use of a unique participant study pseudonym on all study documents and any electronic database. All documents will be stored securely on the University of the West of England One Drive in password – protected folders and will only be accessible by study staff. The CI will safeguard the privacy of participants' personal data.

The personal details that will be collected from the participants will include name, surname, email, phone number so that the CI will have a way to contact participants for the

intervention implementation and the collection of data arrangements. No other members of the research team will have access to participants' personal details. In the event that the CI and the group intervention facilitator assess that participants or others are at serious risk then the care professional who referred them to the study will be contacted to discuss further steps.

### ***Conflict of interest***

The roles of each member of the research team are clearly defined. The CI is the lead researcher of the study and is not involved in the implementation of the group psychological intervention MyMS-Ally or the collection of the qualitative data. The group facilitator will be a trained practitioner who will be supervised by a senior practitioner and they will comprise the clinical team of the study who will not be involved in the collection and analysis of the data. The qualitative interviews will be conducted by an experienced independent researcher. Therefore, research and clinical processes are clearly separated in the course of the study. The CI's identity as a Chartered Counselling Psychologist and her clinical skills will be implemented in order to create safe and respectful environments for participants in the processes of intervention implementation and collection of data.

At the end of the study participants will have the opportunity to meet with the CI for check – in meetings should they accept the invitation. The final results of the study will also be fed back to the participants should they accept the report. Data will be stored in the University of the West of England Research Repository and will be reserved there as restricted data accessed by third parties for purposes of review. The participants' personal details will be destroyed according to guidelines.

### **Principal question/ objective**

The study aims to explore the feasibility and acceptability of the novel group psychological intervention MyMS-Ally. This is a mixed method study and collection of data aims to provide insight on relevance, sustainability and adherence to the intervention and study processes (feasibility) as well as the appropriateness of the intervention based on the emotional and cognitive responses, satisfaction and perceived effectiveness (acceptability) based on participants' accounts and experience of the intervention. The findings are aspired

to help make the appropriate modifications before the intervention is further evaluated in future research (Bowen et al., 2009).

## Secondary objectives

The study aims to collect preliminary data on the impact of the intervention on the participants' quality of life, depression, anxiety and emotion regulation. Outcome measures will be administered at baseline, on completion of the intervention, one month and three months follow – up. Change will be recorded in the outcome measures. Participants' perceived change on the experience and management of MS associated to intervention processes will also be explored in the qualitative interviews. Clients' perspectives offer a significant insight on the impact of psychological intervention processes and effectiveness ([name] et al., 2021).

